### Effectiveness outcomes and study measures

2.5

Participants will complete enrollment and baseline data collection before being randomly allocated the assignment to one of the two study arms. Participants will receive a random assignment through the prepared envelopes to Treat4All or UC at a ratio of 1:1. Masking of participants and intervention counselors to study arm assignment in the field is not feasible because of the nature of the interventions; data collection staff, analysts, and investigators will be masked to the study assignment until analyses are complete. Participants will be followed up for 6 months (Table 1).

**Table 1 tab1:** Schedule of enrollment, interventions, and assessments.

Timepoint	Enrollment	Baseline	Allocation	Post-allocation		
	*t_0_*	*t_0_*	*t_0_*	*t_0_*	Month 3	Month 6
Enrollment						
Eligibility screen	X					
Informed consent	X					
Random group allocation			X			
Intervention						
Treat4ALL						
Usual care						
Assessments						
Quantitative survey						
Sociodemographics and alcohol coping skills		X				
Readiness to change alcohol use Social desirability, sexual risk, HIV testing history, PrEP use history, PrEP knowledge and willingness, and ART initiation		X			X	X
HIV-related stigma, depression, health status, quality of life					X	X
Qualitative interviews (Treat4All arm only)						X
Primary outcomes						
Heavy drinking days (TLFB)		X			X	X
Engagement in HIV prevention (PrEP use) or treatment (viral suppression)		X				X
Secondary outcomes						
All participants						
PEth level^*^		X				X
STI prevalence		X				X
People with HIV only						
Viral suppression		X				X
ART adherence		X			X	X
People at risk for HIV only						
PrEP use		X				X
HIV incidence						X

^*^Dried blood spots will be collected from all participants.

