The baseline questionnaire is a quantitative assessment that will be performed before arm allocation with participants by trained field staff and completed safely in a confidential place. The survey will be administered to gather information on alcohol use, including self-reported percentage of heavy drinking days measured by the timeline followback (TLFB),readiness to change alcohol use, alcohol coping skills, sociodemographics, social desirability, sexual risk, HIV testing history, PrEP use history, PrEP knowledge and willingness, ART initiation, and self-reported ART adherence. Before the start of the RCT, we will pilot the baseline survey and administration procedures with up to 40 people with similar characteristics to our target population (*n* = 20 PWH; *n* = 20 people at risk for HIV). The pilot will be assessed for survey length and checked for response distribution, item comprehension, and data-collection procedures.

Participants will also complete a series of laboratory assessments at baseline. (1) Urine samples will be collected from all participants with consent and tested for the presence of chlamydia, gonorrhea, or syphilis. (2) Blood samples will be collected from all PWH and sent to the UNC Project Malawi laboratory to assess HIV-1 RNA levels using the Abbott RealTime HIV-1. (3) Finger-stick dried blood spots (DBS) will be collected from all participants for phosphatidylethanol (PEth) testing to detect alcohol use during the 21 days before the study visit (48–50). Samples will be kept in a dry box with a humidity indicator card to monitor the moisture levels until they are brought to the laboratory. Samples will be taken to the local laboratory for storage and shipment processing. PEth is detected in whole blood by an LC–MS/MS assay using dried blood spots (United States Drug Testing Laboratories, Des Plaines, IL, USA). PEth is specific to alcohol metabolism, and slow degradation allows alcohol detection for ~21 days. PEth levels are useful for detecting changes in drinking habits within a participant over time. In 2022, the Society of PEth Research (PEth-NET) produced a 2022 Basel Consensus Document recommending a whole blood PEth cutoff concentration of 20 ng/mL as strongly suggestive of drinking more than minimal amounts (50).

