### Data analysis

3.1

We will first explore the distribution of continuous and categorical baseline variables using descriptive statistics and graphical representations, as appropriate (60). We will then conduct intent-to-treat comparisons between arms, using a log link and binomial error distribution to compare the proportion of heavy drinking days and engagement in HIV prevention or treatment (co-primary outcomes). For the proportion of heavy drinking days, we will estimate the self-reported percentage of heavy drinking days measured by the TLFB at 6 months. We will evaluate the extent to which mean values differ across groups using the deviance χ^2^ (61). As the effect of the intervention may differ by age and sex, effect modification by these factors will be examined. For successful engagement in HIV prevention or treatment, the design effect introduced by participant randomization will be addressed using a robust variance estimate. Probability ratios (PR), analogous to prevalence ratios at a specific time point, with 95% confidence intervals, will be used to estimate and compare the proportion of participants in each arm who achieved the outcome (successful engagement in HIV prevention or treatment) at 6 months. All analyses will also be sex-stratified to explore differences by sex to inform power calculations for a future implementation effectiveness trial. A significance level of 0.05 and two-sided 95% CIs will be used with no adjustment for multiple testing (62).

Additional analyses will assess self-reported ART adherence (among PWH), biologically confirmed HIV incidence (among HIV-negative participants), PrEP use (among HIV-negative participants), viral suppression (among PWH), and biologically confirmed STIs (among all participants). We will also assess the possibility of selective differential attrition across the arms at each post-baseline visit. We will estimate and compare an *a priori* set of baseline demographics by the study arm. If an imbalance is found, we will produce post-baseline regression-adjusted outcome estimates by recalibrating the baseline distribution of that group to the baseline distribution across all groups combined (63).

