### Power considerations and sample size calculations

3.2

Our study will provide short-term efficacy data to inform a future, large-scale RCT. All tests will be based on a nominal 5% two-sided type I error, and confidence intervals will have a nominal 95% coverage. The main analysis on which our sample size calculation for the quantitative analysis was based is the short-term efficacy of the experimental intervention, Treat4All, vs. UC. Using two-tailed tests and *α* = 0.05, we will have >80% power to detect a difference as small as 16% points (e.g., 80% vs. 96%) with a sample of 144. To account for possible loss-to-follow-up/dropout of 10% based on our previous studies among patients receiving STI care in Malawi, we will inflate the sample size to 160 (*n* = 80 per arm [stratified 1:1 by HIV status]). While a sample size of 160 may limit generalizability, it is appropriate for this pilot study, which aims to assess feasibility and estimate effect sizes to inform a future, fully powered trial, in line with established guidance for early-phase research and prior pilot studies in similar contexts (64, 65). Sample size calculations were conducted using SAS 9.4, which will also be used for all statistical analyses.

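### The heavy-drinking-days comparison names no baseline covariate, and the only stated adjustment waits for an observed demographic imbalance; prespecified adjustment for baseline drinking and HIV status would gain precision at no data cost

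*Protocol article*

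**What the plan says.** All references are to the protocol article.

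- **Baseline measurement.** Section 2.5 puts into the pre-allocation survey the "self-reported percentage of heavy drinking days measured by the timeline followback (TLFB"). The same section sets one recall window, 21 days, for baseline, month 3 and month 6. Table 1 lists heavy drinking days at all three visits.
- **Primary comparison.** Section 3.1 describes intent-to-treat comparisons of arms with a log-link binomial model, using the month-6 timeline followback value for heavy drinking days. It names neither baseline drinking nor HIV status as a covariate.
- **Adjustment.** Later in section 3.1, in the paragraph on additional analyses and directly after a sentence on differential attrition, the plan compares an a priori "set of baseline demographics by the study arm". It continues: "If an imbalance is found, we will produce post-baseline regression-adjusted outcome estimates by recalibrating the baseline distribution of that group", the target being the baseline distribution pooled over the arms. Imbalance is not defined. The text does not say whether the adjusted or the unadjusted estimate leads when the rule fires.
- **Stratification.** Section 3.2 gives "80 per arm [stratified 1:1 by HIV status"], and section 2.5 allocates "to Treat4All or UC at a ratio of 1:1".

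**The concern.** A like-for-like baseline value of the outcome is planned for every participant before allocation. It is normally among the better predictors of the same measure six months later, and using it removes between-person variation from the arm contrast. As described, the primary comparison makes no use of it.

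The stated route to adjustment does not fill the gap. It is tied to demographics, and by its plain wording that set would not include drinking. It also depends on what the data show. At randomisation, baseline differences between arms arise by chance, so an imbalance check is a poor guide to which covariates to adjust for: the precision gain comes from how strongly a covariate predicts the outcome, whether or not the arms happen to differ on it.

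At stake is the width of the interval around one co-primary estimate, in a pilot whose stated purpose (section 3.2) includes estimating effect sizes for a larger trial.

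**Working it through.** **Inputs from the article.** Two-sided 5% level ("A significance level of 0.05 and two-sided 95% CIs will be used with no adjustment for multiple testing"); "we will have >80% power to detect a difference as small as 16% points (e.g., 80% vs. 96%) with a sample of 144"; an allowance of 10% for attrition; 80 randomised per arm. Equal allocation makes 72 evaluable per arm.

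**Input not in the article.** The correlation r between baseline and month-6 proportion of heavy drinking days. Assumed range: 0.2 to 0.6.

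**1. The plan's own figure.** For 80% vs 96% with 72 per arm, the mean proportion is 0.88.
- z = [0.16 × √72 − 1.960 × √(2 × 0.88 × 0.12)] / √(0.80 × 0.20 + 0.96 × 0.04) = (1.358 − 0.901) / 0.445 = 1.03, so power is 84.8%.
- Variants: arcsine 88.2%, Fisher exact 82.0%.
- Inflation: 144 / 0.9 = 160.

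The stated power and sample size reproduce without any covariate adjustment.

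**2. Gain from always adjusting.** In a linear model, adjusting for a baseline with correlation r multiplies the variance of the arm contrast by 1 − r². Then:
- equivalent sample size = 144 / (1 − r²);
- detectable difference at 80% power = (1.960 + 0.842) × √(2/72) × √(1 − r²), which is 0.467 SD unadjusted;
- power for an effect that has 80% power unadjusted = Φ[2.802 / √(1 − r²) − 1.960].

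| Assumed r | Variance factor | Equivalent of 144 | Detectable difference (SD) | Power |
|---|---|---|---|---|
| 0.2 | 0.96 | 150 | 0.457 | 82% |
| 0.3 | 0.91 | 158 | 0.445 | 84% |
| 0.4 | 0.84 | 171 | 0.428 | 86% |
| 0.5 | 0.75 | 192 | 0.404 | 90% |
| 0.6 | 0.64 | 225 | 0.374 | 94% |

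The base is the 144 evaluable participants, since those are the ones expected to contribute a month-6 value.

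**3. Does conditional adjustment recover the gain?** Simulation: 20,000 runs, 72 per arm, standardised continuous outcome, true effect 0.467 SD. The trigger was set generously to baseline drinking itself differing at p < 0.05. The article states no such trigger, so this is an assumption. To show the trend, r goes up to 0.7.

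| Assumed r | Power: never adjust | Power: adjust if imbalanced | Power: always adjust | Type I error: adjust if imbalanced |
|---|---|---|---|---|
| 0.3 | 79.2% | 79.5% | 82.8% | 5.0% |
| 0.5 | 79.3% | 80.3% | 89.0% | 4.3% |
| 0.7 | 79.4% | 81.1% | 97.1% | 3.7% |

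The conditional rule recovers little of the gain. It does not inflate type I error; at higher r it is slightly conservative.

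**4. How often chance would fire a demographic trigger.** If k independent variables were each tested at 5% (again assumed), the probability is 1 − 0.95^k: 14% for k = 3, 23% for k = 5, 34% for k = 8.

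**The case against.** Much of the case on the other side stands, and it limits the point.

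- **Silence is not exclusion.** A reader might infer that the plan deliberately leaves baseline drinking out of the model. The article never calls the comparison unadjusted and does not rule out a covariate. An analysis plan that is not shown may add one. What can be said is that the model as described has no baseline term, and that the only adjustment rule written down depends on the data.
- **The conditional sentence may be supplementary.** A reader might infer that the primary estimate switches from unadjusted to adjusted once an imbalance appears. The text does not say that. The sentence sits under additional analyses, next to attrition, and can be read as standardising the retained samples. On that reading the imbalance need not be chance, and the recalibration has its own purpose. Section 3.1 also promises weighted and unweighted results side by side for missing data, which suggests that supplementary reporting is the habit.
- **No bias or error-rate failure.** A reader might infer that a chance difference in baseline drinking makes the primary estimate wrong. The unadjusted contrast is unbiased over randomisation and its confidence interval already allows for such differences. The simulation shows no type I inflation.
- **The gain is uncertain.** Every r is assumed, and 1 − r² comes from a linear model while the stated model is log-binomial. Eligibility requires recent heavy drinking, which may narrow the baseline range and lower r. Replacing some self-reports with 50% in the biomarker subsample (section 2.5) could lower it further. At r of 0.2 to 0.3, power rises only from 80% to 82–84%.
- **Scope.** The gain concerns heavy drinking days. For engagement in HIV prevention or treatment, eligibility already restricts baseline status, so a baseline value of that outcome would probably add little.

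None of this gives a reason to prefer the unadjusted contrast, or an imbalance trigger, when the baseline value is already in hand.

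**Conclusion.** The point holds as a precision improvement, not as an error that invalidates the primary analysis. As described, the heavy-drinking-days comparison does not use a baseline measurement planned for every participant or the HIV-status stratum, and the only adjustment stated depends on an observed demographic imbalance that is left undefined.

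For an assumed correlation of 0.2 to 0.6, prespecified adjustment for baseline drinking would cut the variance by about 4 to 36%, so that 144 evaluable participants would be worth about 150 to 225. The gain is small at the low end and material from about 0.5. These figures rest on the assumed correlation and the linear approximation. They cover baseline drinking alone; any contribution from HIV status is not quantified. The plan's stated power does not depend on the change.

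**What to change.** In section 3.1, or in the analysis plan before unmasking:

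1. Name the baseline proportion of heavy drinking days (the same 21-day measure) and HIV status as covariates in the heavy-drinking-days model, whatever balance is observed. Sex may be added if wanted.
2. Report the marginal (standardised) arm contrast from that model as the primary estimate, and the unadjusted contrast as a sensitivity analysis.
3. State that an observed baseline imbalance does not decide which estimate is primary, and keep the baseline comparison by arm as description.
4. If the recalibration is kept for imbalance or attrition, label it supplementary and define what triggers it.

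The cost is wording and a few lines of analysis code. No new data, visits or participants are needed, because the baseline measure and HIV status are already collected before allocation.

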### Power considerations and sample size calculations

3.2

Our study will provide short-term efficacy data to inform a future, large-scale RCT. All tests will be based on a nominal 5% two-sided type I error, and confidence intervals will have a nominal 95% coverage. The main analysis on which our sample size calculation for the quantitative analysis was based is the short-term efficacy of the experimental intervention, Treat4All, vs. UC. Using two-tailed tests and *α* = 0.05, we will have >80% power to detect a difference as small as 16% points (e.g., 80% vs. 96%) with a sample of 144. To account for possible loss-to-follow-up/dropout of 10% based on our previous studies among patients receiving STI care in Malawi, we will inflate the sample size to 160 (*n* = 80 per arm [stratified 1:1 by HIV status]). While a sample size of 160 may limit generalizability, it is appropriate for this pilot study, which aims to assess feasibility and estimate effect sizes to inform a future, fully powered trial, in line with established guidance for early-phase research and prior pilot studies in similar contexts (64, 65). Sample size calculations were conducted using SAS 9.4, which will also be used for all statistical analyses.

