## Introduction

1

Forty years into the HIV epidemic, people living in sub-Saharan Africa (SSA), including Malawi, continue to experience a disproportionate burden of HIV infection. In Malawi, HIV prevalence among adults aged 15–49 is 6.7%, with new infections ongoing (10,000 persons/year; HIV incidence rate of 0.98/1,000 adults), and nearly 30% of people with HIV (PWH) remaining virally unsuppressed (1). Non-HIV sexually transmitted infections (STIs) are common among PWH and those at high risk of HIV and are a marker of condomless sex, multiple partners, high-risk sexual networks, increased vulnerability to HIV, undiagnosed and unsuppressed HIV, and increased viral shedding (among PWH) (2–6). In our prior work, HIV prevalence among people receiving STI care in Malawi was 22% (7). Among people with STI/HIV co-infection in the largest STI clinic in the capital of Malawi, 72% were either newly diagnosed with HIV or previously diagnosed and not on antiretroviral therapy (ART) (8). People with an STI are a priority target population for interventions to improve HIV prevention and treatment. Given this context, people with an STI represent a key population for interventions that improve HIV prevention and treatment.

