### Eligibility criteria

2.3

In coordination with the STI Clinical Director, we will host clinic meetings to introduce the project and study plans to clinical patients. Patients receiving STI care will be provided with information about the project by clinic staff, and those interested will be screened by clinic staff for eligibility.

Patients receive routine opt-out HIV testing as part of their usual care (UC). To be eligible, patients must: (1) be aged 18 or older, (2) be receiving care at the Bwaila STI clinic, (3) report recent heavy drinking (≥4 drinks a day in the past 30 days for men and ≥3 drinks a day in the past 30 days for women), (4) be willing to receive an HIV test at study enrollment, (5) report not taking ART or having a recent history of unsuppressed viral load (>1 viral load test with >40 copies of HIV-1 RNA per milliliter in the past 2 years) [for PWH] *or* not currently taking a PrEP prescription (self-reported taking <1 pill per week) [for those at risk of HIV], (6) plan on residing in Lilongwe for the next 6 months, (7) not participating in other HIV or alcohol programs, (8) ability and willingness of participant to provide informed consent, and (9) willingness to provide contact/locator information to be contacted for follow-up study activities.

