If >10% of observations are missing for a particular endpoint, we will quantify the sensitivity of our results to our assumption that all missing values have not achieved the outcome of interest (i.e., they did not decrease heavy drinking or did not achieve HIV outcome). We will assess predictors of loss to follow-up and apply inverse probability of observation weights (IPOW) to assume that data are missing at random (MAR). When disseminating the results, we will present weighted and unweighted results and a description of the accompanying assumptions.

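### The claim of more than 80% power for a 16-point difference holds only if the usual-care rate is about 78% or more, or about 5% or less, and the endpoint it refers to is not named

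*Protocol article*

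**What the plan says.** The power section sets the error rate, "All tests will be based on a nominal 5% two-sided type I error", and then states that "we will have >80% power to detect a difference as small as 16% points (e.g., 80% vs. 96%) with a sample of 144". It allows for "possible loss-to-follow-up/dropout of 10" per cent, so "we will inflate the sample size to 160", that is 80 per arm, stratified equally by HIV status. Allocation is to "Treat4All or UC at a ratio of 1:1" (Effectiveness outcomes and study measures). The calculation is tied only to short-term efficacy against usual care. It names no endpoint and gives no source for the 80%.

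There are two co-primary outcomes: the proportion of heavy drinking days at month 6, and engagement in HIV prevention or treatment. Engagement pools viral suppression in people with HIV (PWH) with PrEP use in those at risk. Under Eligibility criteria, PWH must be off ART or have a recent history of unsuppressed viral load, and at-risk participants must be "not currently taking a PrEP prescription (self-reported taking <1 pill per week"). The Introduction gives, for Malawi as a whole, "nearly 30% of people with HIV (PWH) remaining virally unsuppressed".

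**The concern.** The sentence presents 16 points as the trial's detectable difference and 80% against 96% as one illustration of it. For two proportions, the power for a fixed difference depends strongly on where the rates lie. It is highest near 0% or 100% and lowest around the middle. The illustration sits near the top, where 16 points is easiest to detect.

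That position is also awkward for this trial. Participants are selected because they lack the outcome, or recently lacked it, at entry. If usual-care engagement at 6 months is well below 80% but not close to zero, the stated power is not available. A null result could then be read as evidence against a 16-point effect when the chance of detecting one was about one in two. In addition, a reader cannot tell which co-primary outcome the figure covers. A comparison of two percentages does not by itself give the power for a mean proportion of days.

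**Working it through.** **Inputs.** Two-sided alpha 0.05; 144 analysed with 1:1 allocation, so n = 72 per arm; difference d = 0.16; example rates 0.80 and 0.96; 10% loss (all from the protocol article).

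**Formula.** Two-proportion z test with pooled variance under the null, where p̄ is the mean of the two rates:

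power = Φ{ [d − 1.96·√(2p̄(1−p̄)/n)] / √([p₁(1−p₁) + p₂(1−p₂)]/n) }

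**The plan's own figure.** p̄ = 0.88. The null standard error is √(2 × 0.88 × 0.12/72) = 0.0542, and 1.96 × 0.0542 = 0.1062. The alternative standard error is √((0.16 + 0.0384)/72) = 0.0525. Power = Φ((0.16 − 0.1062)/0.0525) = Φ(1.03) ≈ 0.85. Exact enumeration gives 0.88 for the chi-square test and 0.82 for Fisher's test. Inflation: 144/0.9 = 160. The example and the inflation both reproduce.

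**The same 16-point increase at other usual-care rates, n = 72 per arm:**

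| Usual-care rate | Power for +16 points | Difference with 80% power (points) |
|---|---|---|
| 4% | 85% | 14.7 |
| 5% | 82% | 15.4 |
| 10% | 71% | 18.2 |
| 20% | 57% | 21.4 |
| 25% | 53% | 22.2 |
| 30% | 51% | 22.8 |
| 42% | 48% (minimum) | 23.1 |
| 50% | 49% | 22.6 |
| 60% | 54% | 21.1 |
| 70% | 64% | 18.7 |
| 75% | 73% | 17.2 |
| 78% | 80% | 16.1 |
| 80% | 85% | 15.3 |

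For example, at 30% against 46%: p̄ = 0.38, 1.96 × √(2 × 0.38 × 0.62/72) = 0.1586, alternative standard error 0.0798, and power = Φ(0.0014/0.0798) ≈ 0.51.

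**Is 80% engagement under usual care plausible?** The two HIV strata are equal in size, so the pooled rate is (suppression + PrEP use)/2.
- With every PWH suppressed, a pooled 80% needs 2 × 80 − 100 = 60% PrEP use.
- With 70% suppressed (100 − 30 from the Introduction, taken as an assumption for this group), it needs 2 × 80 − 70 = 90% PrEP use.
- A pooled 96% under Treat4All needs at least 2 × 96 − 100 = 92% in each stratum.

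**Other usual-care scenarios (all assumed).**
- 70% suppression with 0–50% PrEP use pools to 35–60%, with power 49% and 54% at the two ends and a minimum of 48% in between.
- 30% suppression with 10% PrEP use pools to 20%, with power 57%.
- 10% suppression with no PrEP use pools to 5%, with power 82%.

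**Heavy drinking days.** Treated as a mean proportion per participant, the difference with 80% power is (1.96 + 0.84) × SD × √(2/72) ≈ 0.467 × SD. The article gives no SD. Assumed SDs of 25 and 40 points give about 12 and 19 points. Sixteen points has 80% power if the SD is about 16/0.467 ≈ 34 points or less.

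**The case against.** The arithmetic in the article is correct for the rates it prints, and those rates are visible to the reader. The trial is called a pilot meant to assess feasibility and estimate effect sizes, so modest power is no fault in itself. All of this stands. Pilot status excuses low power, but it does not make a general power statement true when it holds only in part of the range.

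Four stronger readings are tempting, and the documents do not support them.

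- A reader might infer that the claim holds only at 80% against 96%. It also holds at the low extreme, and strict eligibility could push usual-care engagement that way. Against this, about 5% would need something like 10% suppression and no PrEP use. Usual care includes HIV counselling and referral of PWH to an HIV clinic as needed, and a past unsuppressed viral load is enough for entry. The low extreme is possible, but the protocol does not invoke it.
- A reader might take about 50% as the trial's actual power. No 6-month usual-care rate is given, and the national suppression figure describes all PWH in Malawi, not those enrolled. Over usual-care rates of 10–70%, power runs from 48% to 71%.
- A reader might count dropouts as failures and cut the power further, citing "our assumption that all missing values have not achieved the outcome of interest" under Data analysis. That assumption is examined as a sensitivity analysis when more than 10% of observations are missing, alongside inverse probability weighting. The planned 10% loss does not exceed that trigger, so such a figure would not describe the planned main analysis.
- A reader might say heavy drinking days has no power calculation at all. The endpoint is unnamed, so the calculation cannot be assigned to engagement alone. What can be said is that no inputs suited to a mean proportion of days are given. For this outcome 16 points may well be detectable, depending on the SD.

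**Conclusion.** The concern holds in limited form. The worked example is correct, but 16 points is not a general detectable difference for 144 analysed participants. The stated power needs a usual-care rate of about 78% or more, or about 5% or less. Between 25% and 60% it is 48–54%, and there the difference detectable with 80% power is about 21–23 points. The upper region is hard to square with the eligibility criteria and the pooled definition of engagement, and the article offers no justification for it. The powered endpoint is unidentified, and heavy drinking days lacks a mean or SD.

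The power figures rest on the two-proportion normal approximation with 72 per arm. Where the true usual-care rate lies remains an assumption, and so does any SD for heavy drinking days.

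**What to change.** Keep 160 participants and revise the power section as follows.

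- Name the endpoint to which the calculation refers.
- State the assumed 6-month usual-care engagement rate and justify it against the eligibility criteria, separately for PWH and those at risk before pooling.
- Replace the single 16-point claim with a range. With 72 analysed per arm and a two-sided 5% test, the difference detectable with 80% power is about 18 points at a usual-care rate of 10%, 21 at 20%, 21–23 at 30–60% and 19 at 70%. A 16-point difference has roughly 50% power at rates of 25–60%. These rates should be labelled as a grid of scenarios, not as expected values, unless they can be sourced.
- Give heavy drinking days its own detectable difference with a stated and sourced SD (about 12–19 points for assumed SDs of 25–40 points), or drop the power claim for that outcome.

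The cost is a less favourable set of stated figures. Sample size, procedures and analyses do not change.
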